### Phase III: study design

This is a multicenter, national prospective two-arm RCT of Couplelinks. Approximately 80 eligible couples will be randomized to either the treatment condition or a waitlist control condition, using randomized block design with a block size of 2 (1:1), stratified by province of residence. The randomization list is generated using PROC FACTEX in SAS (Statistical Analysis System) version 9.3, SAS Institute, Cary, USA.

This study was approved by the Research Ethics Boards of all participating hospitals and cancer centers, namely Sunnybrook Health Sciences Centre (reference number: 300–2009), York University (reference number: 2010-119), Cancer Care Manitoba - Research Resource Impact Committee (reference number: 2013–017), University of Manitoba (reference number: H2013:119), University of British Columbia - British Columbia Cancer Agency Research Ethics Boards (reference number: H10-00300), and Queen Elizabeth II Health Sciences Centre - Capital Health Research Ethics Board (reference number: CDHA-RS/2010-357).

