Next, each partner is separately emailed a unique personal login ID and password which they use to complete all questionnaires, starting with the baseline questionnaires. The couples in the treatment group complete additional questionnaires as described in the measurement section below. Participants are informed that their responses to the surveys will not be shared with their partner, and they are instructed to complete the surveys without consulting one another. Once the time one (T1) measures are completed, the RC informs participants of their group assignment. Participants assigned to the treatment group are informed of the name of their Couplelinks facilitator. The facilitator schedules a phone meeting with the couple to introduce her or himself, clarify expectations of participants, answer questions, and review important information about the website and the intervention. The facilitator then sends the couple their login instructions via email.

Both groups of participants complete standardized questionnaires online at T1, time two ((T2) at post-treatment for treatment and for waitlist groups, taking place eight weeks after T1), and time three ((T3) three months after completion of T2 measures). Participants in the treatment group are also asked to complete a post-treatment interview at T2. Couples in the waitlist group are given the option of receiving the intervention once they have completed the T3 questionnaires; if they choose to participate in the intervention, their completed T3 questionnaires will be used as their pre-treatment (baseline) measurement, and they will be asked to complete surveys at post-treatment and one last time 3 months after posttreatment.

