The Hospital Anxiety and Depression Scale (HADS) [103] is a 14-item four-point Likert scale measure that includes two subscales of seven items each, assessing anxiety and depression. It is a simple yet reliable and valid tool to assess the presence of a mood disorder in medical settings. Although developed for a hospital-based population, it has also been found to be a valid screening instrument for depression and anxiety in the general population [104]. The Functional Assessment of Cancer Therapy-Breast (FACT-B) - Physical Well-Being (PWB) [105] subscale is part of the widely used FACT-B that assesses quality of life among breast cancer patients. The PWB, a seven-item five-point Likert scale measuring physical functioning, is completed by the female partner only. This variable will be tested as a potential covariate. The Breast Cancer and Relationship Measure (BCRM) was developed by the study authors for this protocol to assess the degree to which partners experience breast cancer to have negatively affected their relationship. The scale has 10 items which participants rate on a scale from 0 (not at all) to nine (very much) depending on the degree to which each statement applies to them. An example item is ‘We are able to discuss difficult or sensitive issues related to breast cancer’.

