### Sample size estimation and data analyses plan

All scale and subscale means and standard deviations will be computed and summarized. The primary hypotheses to be tested are that the degree of change or improvement between T1 and T2 on the RDAS, KMSS, MMQ, and DCI summary scales will be greater for the treatment group relative to the waitlist group. Given that data are non-independent (measurements are of individuals that belong to the same dyad and multiple measures are taken per individual across time) the hypotheses will be evaluated using multilevel models (MLM) [109]. MLM will allow for testing correlations between partners’ outcomes and whether there are differences in treatment effect for the patient versus her partner. The models will also be used to evaluate the degree of sustained change from T2 to T3, and whether treatment effects vary by severity of disease, age, and/or length of relationship, as well as aspects of the intervention such as level of engagement. MLM will also allow us to test whether there are any significant variations in treatment effect between facilitators. The impact of missing data will also be evaluated.

The sample size needed was based upon psychometrics of our primary outcome measure, the RDAS. Assuming a two-sided test, a standard deviation for mean change in RDAS from T1 to T2 equal to 3.4 (standard deviation of RDAS = 7.0, with a correlation of 0.9 between T1 and T2), an intracluster correlation of 0.3, an effect size of 0.5 for mean change of RDAS (difference in group means = 1.8), 80% power, and an alpha of 0.05, 36 couples will be required for each group (PASS, NCSS, Kaysville, USA, cluster-randomization power analysis) [110]. The total sample size was calculated as 36 × 2 × 2 = 144. The sample size will be increased to 160 (40 couples per group) due to an expected attrition of 10% of the participants across time, based on previous research in couples and BC [111]. In addition to the questionnaires, qualitative data will be collected from the open-ended evaluation of each DLM following its completion.

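### Durability is framed as T2-to-T3 change with no arm difference named at T3; the planned multilevel model can report T1-adjusted arm differences at T2 and T3 at no cost

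*Protocol article*

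**What the plan says.** Under Sample size estimation and data analyses plan, the primary hypotheses are that "the degree of change or improvement between T1 and T2 on the RDAS, KMSS, MMQ, and DCI summary scales will be greater" in the treatment arm than in the waitlist arm. Because the data are dyadic and repeated, "the hypotheses will be evaluated using multilevel models (MLM"). The trial is sized on the SD of RDAS change from T1 to T2.

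Durability gets one clause: "The models will also be used to evaluate the degree of sustained change from T2 to T3". No between-arm contrast at T3, and none from T1 to T3, is named.

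Three other places bear on this:

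- **Procedure:** both arms are assessed at T3, three months after T2. Waitlist couples are "given the option of receiving the intervention once they have completed the T3 questionnaires", so they are still untreated when T3 is measured.
- **Phase III: study design:** allocation is in blocks of 2, "stratified by province of residence".
- **Measurement:** of FACT-B physical well-being, "This variable will be tested as a potential covariate". The note to Figure 1 lists FACT-B among the outcome questionnaires.

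**The concern.** The durability question is whether couples offered the programme are still better off than untreated couples three months later. The contrast named runs from T2 to T3, which is a different quantity. If it is taken within the treatment arm, it leaves the randomised comparison aside. If it is taken between arms, it measures how much the effect moved, not how large it is at T3. A small or non-significant movement is easily mistaken for evidence of maintenance, and with this sample size quite large losses would look small.

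A lesser matter is precision. A contrast of change from T1, with no further adjustment, is less precise than one adjusted for T1 whenever the T1-T2 correlation is below 1 and the variances are equal. Province was used in the randomisation and belongs in the model. The covariate wording leaves open whether physical well-being enters, and at which time point.

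**Working it through.** **Inputs, all from Sample size estimation and data analyses plan.** SD of RDAS 7.0; T1-T2 correlation 0.9; SD of change 3.4; intracluster correlation 0.3; difference 1.8; two-sided alpha 0.05; power 80%; 36 couples per arm, 40 after 10% attrition.

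**1. The plan's own figure.** Individuals per arm = 2 × (3.4 × (1.960 + 0.842) / 1.8)² = 56.0. With design effect 1 + (2 − 1) × 0.3 = 1.3 and two partners per couple, 56.0 × 1.3 / 2 = 36.4 couples, against 36 stated. Normal-approximation power at 36 couples is 79.6%. Attrition: 36 / 0.9 = 40. The stated size reproduces.

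**2. What the T2-to-T3 contrast estimates.** Let D2 and D3 be the arm differences at T2 and T3. The between-arm T2-to-T3 contrast is D3 − D2.

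| Situation | D2 | D3 | D3 − D2 |
|---|---|---|---|
| Effect fully kept | 1.8 | 1.8 | 0 |
| Never an effect | 0 | 0 | 0 |
| Half the effect lost | 1.8 | 0.9 | −0.9 |

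The first two rows cannot be told apart by D3 − D2. D3 separates all three.

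**3. How precise that contrast is.** The article gives no SD for T2-to-T3 change. Assume 3.4 and the same intracluster correlation.

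- SE = 3.4 × √(2 × 1.3 / 72) = 0.646, with 72 individuals (36 couples) per arm.
- 95% CI half-width = t(70 df) × SE = 1.994 × 0.646 = 1.29 points.
- Power to detect a loss of 0.9 points: noncentrality 0.9 / 0.646 = 1.39, giving 0.28.

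Losing half the benefit would therefore go undetected about 72% of the time.

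**4. What T1 adjustment would gain.** With equal variances at T1 and T2, the variance of change is 2(1 − r)σ² and the T1-adjusted variance is (1 − r²)σ². Their ratio is (1 + r)/2. The stated correlation and the stated change SD differ slightly: r = 0.9 gives 7.0 × √0.2 = 3.13, while 3.4 implies r = 1 − 3.4²/98 = 0.882. Both are shown. Power is by normal approximation at 36 couples per arm, with an intracluster correlation of 0.3 kept for both analyses.

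| r | Change SD | Adjusted SD | Variance ratio | Power, change | Power, adjusted |
|---|---|---|---|---|---|
| 0.9 (stated) | 3.13 | 3.05 | 0.95 | 85.7% | 87.4% |
| 0.882 (implied by 3.4) | 3.40 | 3.30 | 0.94 | 79.6% | 81.9% |
| 0.8 (assumption) | 4.43 | 4.20 | 0.90 | 57.1% | 61.6% |
| 0.7 (assumption) | 5.42 | 5.00 | 0.85 | 41.6% | 47.4% |

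**5. Province.** The article gives no between-province variance, so this gain cannot be computed.

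**The case against.** The best reply is that the article specifies a repeated-measures multilevel model. Such a model can hold T1 means equal across arms, or take T1 as a covariate, and it can produce an arm difference at T3. All hypotheses are framed against the control condition, and both arms are measured at T3, so the right comparison may well be intended. The T1-to-T2 test also comes first, so the case of no effect at any time would normally be caught there.

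Much of this stands. A reader might infer that raw change scores will be analysed, that the model cannot show a lasting effect, or that a non-significant T2-to-T3 result will be declared proof of maintenance. The text says none of these. Sizing on a change SD does not commit the analysis to change scores, and the word degree can be read as estimation. Nor does silence on T1 and province terms in a condensed article amount to a decision against them. Likewise, nothing says that later values of physical well-being will be used as a covariate.

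What does not fall away is the contrast that is named. A clear T1-to-T2 effect followed by a T2-to-T3 interval of about ±1.3 points still leaves the T3 effect unstated, and the first test does nothing to reveal a later loss of half the benefit.

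**Conclusion.** The point holds as a free improvement in the stated contrasts; it is not a fault in the model. The only durability contrast described estimates D3 − D2, which by itself cannot show that benefit persists, while a randomised comparison at T3 is available from data already being collected. The figures of about ±1.3 points and 28% power rest on carrying the 3.4 change SD and the 0.3 intracluster correlation over to the T2-to-T3 interval, with 36 couples per arm.

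The precision argument is secondary. On the article's own figures, T1 adjustment saves about 5 to 6% of variance, or roughly two points of power. It would be worth 10 to 15% of variance only if the true correlation were 0.8 or 0.7, which is an assumption. The benefit of including province cannot be quantified.

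**What to change.** Within the planned multilevel model:

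- Use a common T1 mean across arms, or T1 as a covariate, and include province as a fixed factor.
- Name the between-arm difference at T2 as the primary contrast and the between-arm difference at T3 as the durability contrast, each with a 95% confidence interval. Give T2-to-T3 change descriptively.
- Decide in advance whether physical well-being is a covariate. If it is, use its T1 value only.

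This changes analysis-plan wording only. It needs no extra visits, data or couples, and costs a few degrees of freedom for province.

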## Discussion

The potential for Couplelinks to fill a void in the support options available to both younger women with BC and their male partners is great. The intervention, if proven effective, will be the first empirically validated online support tool for heterosexual couples with the female partner belonging to the highly distressed and inadequately served population of young BC survivors. Moreover, this validated program will address the consistently demonstrated need for targeted resources that appeal to their male partners. If effective, this standardized psychosocial intervention can be readily incorporated into existing psychosocial oncology programs, with the added benefit of independence from geographic disparities. Moreover, as one of the first couple interventions of its kind, Couplelinks will help set a clinical and scholarly precedent for the delivery of online support to couples in distress. The ultimate impact of the study will be the creation of an accessible, empirically validated tool that could help to improve the quality of life of future young couples coping with BC, regardless of geographic location.

Assuming effectiveness is demonstrated, the next step would be to refine the treatment and training manual, and disseminate the program to psychosocial oncology professionals. They, in turn, would have access to the website on a cost-recovery basis in order to offer the program within their own communities and provinces. Furthermore, as an empirically validated prototype, Couplelinks may be adapted for other subgroups of BC survivors and their partners, such as same-sex or middle-aged couples, or for couples dealing with other types of cancer.

## Trial status

Recruitment for this project has been underway since April 2011. The estimated date of completion is June 2015.

## Abbreviations

BC: Breast Cancer
BCRM: Breast Cancer and Relationship Measure
CEQ: Credibility Expectancy Questionnaire
CHESS: Comprehensive Health Enhancement Support System
DCI: Dyadic Coping Inventory
DLM: Dyadic Learning Modules
DR: Dialogue Room
FACT-B: Functional Assessment of Cancer Treatment
HADS: Hospital Anxiety and Depression Survey
KMSS: Kansas Marital Satisfaction Survey
MLM: Multilevel Models
MMQ: Maudsley Marital Questionnaire
RCT: Randomized Controlled Trial
RC: Research Coordinator
RDAS: Revised Dyadic Adjustment Survey
SUS: System Usability Scale
T1: Time One
T2: Time Two
T3: Time Three
TSS: Treatment Satisfaction Survey.
